# Study protocol of a multicenter randomized controlled trial of mindfulness training to reduce burnout and promote quality of life in police officers: the POLICE study

**DOI:** 10.1186/s12888-018-1726-7

**Published:** 2018-05-25

**Keywords:** Mindfulness, Police, Quality of life, Burnout, Stress

## Abstract

**Background:**

Police officers experience a high degree of chronic stress. Policing ranks among the highest professions in terms of disease and accident rates. Mental health is particularly impacted, evidenced by elevated rates of burnout, anxiety and depression, and poorer quality of life than the general public. Mindfulness training has been shown to reduce stress, anxiety, burnout and promote quality of life in a variety of settings, although its efficacy in this context has yet to be systematically evaluated. Therefore, this trial will investigate the efficacy of a mindfulness-based intervention versus a waitlist control in improving quality of life and reducing negative mental health symptoms in police officers.

**Methods:**

This multicenter randomized controlled trial has three assessment points: baseline, post-intervention, and six-month follow-up. Active police officers (*n* = 160) will be randomized to Mindfulness-Based Health Promotion (MBHP) or waitlist control group at two Brazilian major cities: Porto Alegre and São Paulo. The primary outcomes are burnout symptoms and quality of life. Consistent with the MBHP conceptual model, assessed secondary outcomes include perceived stress, anxiety and depression symptoms, and the potential mechanisms of resilience, mindfulness, decentering, self-compassion, spirituality, and religiosity.

**Discussion:**

Findings from this study will inform and guide future research, practice, and policy regarding police offer health and quality of life in Brazil and globally.

**Trial registration:**

ClinicalTrials.gov NCT03114605. Retrospectively registered on March 21, 2017.

## Background

Police officers are routinely exposed to dangerous and unpredictable situations [1]. Exposure to acute and chronic stress is reflected in elevated officer rates of burnout [2, 3], depression [4], suicide [5–7], and anxiety [8]. In addition to higher rates of mental health concerns, police officers have an increased risk of sudden cardiac death, diabetes, obesity and metabolic syndrome [9, 10]. It is no surprise to find that this occupation ranks highest on diseases and accidents rates among all professions [11, 12]. Police quality of life is generally poor [13], including among Brazilian military police [14, 15] and recruits [16]. Brazil has the 7th highest crime index in the world, and Porto Alegre and São Paulo—where participants will be recruited for this study—have the 11th and 14th highest crime index of cities in the world, respectively [17, 18].

Police stress and related mental and physical health consequences can negatively impact work and personal life. Stress-impaired officers are more likely to make serious errors, and exhibit other adverse work outcomes including uncontrolled anger toward suspects, excessive use of force, and absenteeism [19, 20]. The effects of work-related stress also extends to personal life, contributing to disruptive family relationships [21]. It is estimated that approximately one third of police officers meet criteria for burnout syndrome (emotional exhaustion, despersonalization, and low personal accomplishment) [22]. The emotional, physical, economic and social damage of stress in police indicates an urgent call for effective preventive programs to reduce the negative impact of stress and burnout, and to enhance quality of life and well-being.

Mindfulness is an innate meta-awareness capacity to attend to present-moment experience while avoiding entanglement in cognitive biases. It can be enhanced by simple meditative attentional practices, as well as through structured training programs such as mindfulness-based interventions (MBIs). MBIs are generally group-based weekly classes consisting primarily of meditation practices, such as the body scan, mindful movement, sitting and walking meditation. By repeatedly bringing attention back to the current experience, participants gradually learn to disengage from “automatic pilot”, and directly experience emotions and bodily sensations in the present moment. In MBIs, participants learn the ability to step back from ruminating about the past or worrying about the future and simply allow experiences to unfold [23, 24].

Mindfulness training may regulate how the individual appraises stress, and increase secondary appraisals of approach-oriented coping resources, thus reducing stress reactivity. Recent meta-analyses support this theory, indicating MBIs improve common health and risk factors, including stress [25, 26], depression and suicidal ideation [26, 27], anxiety and burnout [28, 29], and increases psychological resilience [30, 31]. MBIs have been shown to be feasible and to lead to improved health outcomes among several high-stress populations, such as military personnel [32, 33], physicians [34, 35], firefighters [36], and inner-city teachers [37].

MBI studies among police officers are limited; however, a pre-post study suggests that mindfulness training can reduce stress and burnout symptoms [38], and findings from a recent RCT indicate that relative to waitlist control, MBI participants experienced greater reductions in salivary cortisol (AUCi), self-reported aggression, burnout, alcohol use, sleep disturbance, and increases in psychological flexibility and non-reactivity at post-training [39]. Despite these promising findings and a global increase among law enforcement agencies integrating mindfulness into trainings, the impact and benefits of MBIs have yet to be systematically evaluated in this context.

### Aims

The aim of the POLICE (imPact Of a mindfuLness-based Intervention on burnout and quality of life in poliCE officers) study is to evaluate the efficacy of a MBI, compared to a waitlist control group, in promoting quality of life and mental health in police officers. We also aim to investigate the feasibility and acceptability of an 8-week, 2-h long MBI on this particular setting.

Our main hypothesis is that mindfulness training will reduce burnout symptoms and improve quality of life. We expect individuals allocated to the MBI group will endorse improved quality of life and reduced burnout (primary outcomes), as well as reduced stress, anxiety, and depression symptoms (secondary outcomes). Potential mechanisms of change include mindfulness, self-compassion, spirituality, decentering, and resilience skills.

## Methods

### Study design

The POLICE study is a multicenter, parallel, two-armed, RCT with 3 assessment points (baseline, post-intervention, and six-month follow-up). Participants will be randomized to MBI or a waiting list control group. This protocol was prepared in accordance with SPIRIT 2013 statement [40] and was approved by the centers ethical committees. The study was registered under ClinicalTrials.gov NCT03114605 on 03/21/17 and will be conducted following the CONSORT guidelines [41]. Figure 1 shows the participant flow through the trial.

**Fig. 1 Fig1:**
[figure not shown]
Study design

### Sample size and power calculations

Power calculations were conducted to determinate the required sample size for the primary outcomes using the statistical software G * Power 3.1.9.2. The minimum sample for each group was identified as 64 to detect a moderate effect size of 0.5 (Cohen’s *d*) with a power of .80 and an alpha of 0.05, based on a previous study [42]. Therefore, the RCT will enroll 160 participants (80 each group) and allow for up to 20% loss to follow-up, expecting a minimum effective sample size of 128 individuals.

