### Primary outcomes measures

*World Health Organization Quality of Life- BREF (WHOQOL-BREF):* the World Health Organization has developed a quality of life instrument, the WHOQOL, which captures many subjective aspects of quality of life. The WHOQOL-BREF is a WHOQOL shorter version, comprises 26 items that produces scores for four domains related to quality of life: physical health, psychological, social relationships and environment. It also includes one facet on overall quality of life and general health. Is one of the best known instruments that has been developed for cross-cultural comparisons of quality of life and is available in more than 40 languages [65]. Evidence consistently shows that officers exhibit low quality of life and its correlation with adverse mental health outcomes [4, 66, 67].*Maslach Burnout Inventory - General Survey (MBI-GS):* is considered one of the leading measures of burnout. Validated by extensive research, MBI-GS Surveys address three dimensions: Emotional Exhaustion measures feelings of being emotionally overextended and exhausted by one’s work; Depersonalization measures an unfeeling and impersonal response toward recipients of one’s service, care treatment, or instruction; Personal Accomplishment measures feelings of competence and successful achievement in one’s work. The MBI-GS is designed for use with occupational groups. The 3 dimensions are distributed in 16 items, whose answers are given on a 7-point Likert scale that varies from “never” to “every day” [68]. Nature and environment of police work contributes to high burnout rates which are associated with escalating symptoms of diminished health [22].

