### Statistical analysis

Intention-to-treat (ITT) and per protocol analyses (PPA) will be conducted following the CONSORT recommendations for reporting the results [41]. Baseline differences between groups on sociodemographic and clinical variables will be assessed using Chi-square tests for categorical variables and analysis of variance (ANOVA) for continuous data. A 2 (Group: MBI vs. WL) × 3 (Time: baseline, post, and 6-month follow-up) repeated measures ANOVA will be conducted to test the effects of the intervention for all primary and secondary outcomes. Effect sizes (Cohen’s *d*) and confidence intervals for within- and between-group comparisons will be performed for each study outcome. Missing data will be handled according to the most appropriate method depending on the reasons for missingness, following the authors’ recommendations and sensitivity analyses principles [80].

To study potential working mechanisms of mindfulness intervention, mediation analysis will be conducted using the Preacher and Hayes (2004) procedure [81]. The mediation effects of mindfulness, self-compassion, resilience, decentering and spirituality on burnout symptoms and quality of life will be evaluated.

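### The sample size for two primary constructs, scored on seven or eight scales, is that of one t-test at 0.05; without a success rule, either the 0.80 power or the 5% error rate does not carry over to the main hypothesis

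*Protocol article*

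**What the plan says.** All references are to the protocol article.

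- **Primary outcomes.** The abstract (Methods) states: "The primary outcomes are burnout symptoms and quality of life". The Aims section joins the two: "Our main hypothesis is that mindfulness training will reduce burnout symptoms and improve quality of life".
- **Their measures.** Under Primary outcomes measures, the WHOQOL-BREF "produces scores for four domains related to quality of life: physical health, psychological, social relationships and environment". The article adds: "It also includes one facet on overall quality of life and general health". For burnout, "MBI-GS Surveys address three dimensions". That makes seven scores, or eight with the overall facet. No burnout total and no lead domain is named.
- **Sample size.** Sample size and power calculations gives one calculation, said to serve the primary outcomes in the plural: "The minimum sample for each group was identified as 64 to detect a moderate effect size of 0.5" (Cohen's d), with power 0.80 and alpha 0.05. Allowing for 20% loss, this becomes 80 per group and 160 enrolled.
- **Analysis.** Under Statistical analysis, a 2 (group) × 3 (time) "repeated measures ANOVA will be conducted to test the effects of the intervention for all primary and secondary outcomes", followed by effect sizes and confidence intervals for each outcome.

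**The concern.** One test has been sized, but the claim the trial wants to make rests on at least two. With two primary constructs and several scores under each, the power and the error rate of the overall claim depend on what counts as success. The article does not say.

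Two things are at stake. If the conjunction in the Aims is meant literally, the chance of achieving it is lower than the 0.80 a reader takes from the sample-size section. If one favourable domain would be enough, the chance of a spurious positive primary result is several times 5%. And while the rule is open, it can be settled after the results are known.

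**Working it through.** **Inputs.** From the article: d = 0.5, alpha 0.05, power 0.80, 64 evaluable per group, 20% loss, three burnout dimensions, four quality-of-life domains and one overall facet. Assumed, because the article does not give them:
- a two-sided test;
- correlations between scores of 0 to 0.7, with all scores oriented so that higher is better;
- a true d of 0.5 on every score when power is computed.

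Each score is treated as one two-group comparison, as in the article's own calculation.

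**1. The article's own figure.**
- Normal approximation: n = 2(1.960 + 0.842)² / 0.5² = 62.8, so 63 per group.
- Noncentral t: 63.77, so 64 per group, with power 0.801 at 64.
- One-sided: 50.15, so 51. This does not match, which supports the two-sided reading.
- Loss: 64 / 0.80 = 80 per group, 160 in total.

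The figure is correct for one test that uses the whole 0.05.

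**2. Rule A: one score per construct, both required at 0.05.** A false claim needs the null score to be significant, so the error rate stays at or below 0.05. Power falls:
- Independent scores: 0.8015² = 0.642 by exact t (0.65 by normal approximation).
- Correlation 0.3, 0.5, 0.7: 0.68, 0.70, 0.72 (simulation, normal approximation; the t-test gives 0.71 at 0.7).
- With no loss at all (80 per group, single-test power 0.8816): 0.8816² = 0.777 if independent.

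**3. Rule B: any one score suffices, no adjustment.** Power for at least one success exceeds 0.80, but the error rate rises:
- Two scores: 1 − 0.95² = 9.75%.
- Seven scores: 1 − 0.95⁷ = 30.2% if independent; 27%, 23% and 18% at correlation 0.3, 0.5 and 0.7 (simulation, 400,000 draws).
- Eight scores: 1 − 0.95⁸ = 33.7% if independent.

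**4. A mixed rule: any burnout score and any quality-of-life score.** The worst case is that one construct truly improves and the other does not.
- Burnout null: up to 1 − 0.95³ = 14.3%, or 11% at correlation 0.7.
- Quality of life null: up to 1 − 0.95⁴ = 18.5%, or 13% at correlation 0.7.

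**5. Either of two named scores, adjusted.** Power at 64 per group:
- Bonferroni, 0.025 each: 0.712 per test.
- Holm, independent scores: 0.712 + (0.801 − 0.712) × 0.712 = 0.775 by these rounded inputs, and 0.776 unrounded. At correlation 0.7 it is 0.76 (simulation).
- Holm, at least one of the two: 0.92 if independent, 0.82 at correlation 0.7.

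**6. Enrolment needed for 0.80.**
- Rule A, independent: single-test power must be √0.80 = 0.894, so 84 per group; 84 / 0.80 = 105, 210 in total.
- Bonferroni over two scores: 78 per group; 78 / 0.80 = 97.5, so 98, 196 in total.

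**The case against.** **The missing rule may be elsewhere.** This is a condensed article and no SAP is shown. A multiplicity procedure, lead domain and success rule may be written there, so their absence from the article is not in itself a fault. That stands. What the article does fix is a sample size for plural primary outcomes whose arithmetic covers one test at full alpha. An SAP can choose the rule, but it cannot make 0.80 the power to succeed on both constructs with 64 per group.

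**The overall facet could serve as a single quality-of-life score.** That is fair. It would reduce the count, but the article does not give it that role, and two constructs would remain.

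**Stronger readings a reader might infer, which the text does not support:**
- *Fourteen tests, seven scores at each of two post-baseline visits, each at 0.05.* The plan is one ANOVA per outcome over all three assessments. The value 0.05 appears only in the sample-size section, and no significance level is attached to the effect sizes and intervals. The count the text supports is seven, or eight.
- *Both the alpha and the power fail.* These losses belong to different rules. Requiring both scores costs power and leaves alpha intact. Accepting any one without adjustment costs alpha and leaves power above 0.80.
- *One significant domain would make the trial positive.* Nothing says so, and the wording of the Aims points to the conjunction.

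**An adjusted either-score rule can keep both properties in one sense.** With Holm over two named scores, the chance of at least one success is 0.82 to 0.92 if d = 0.5 holds for both. This is correct, but it requires naming the two scores, and the power for each score is then 0.76 to 0.78.

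**Conclusion.** The point holds in this limited form. The 64 per group and 160 enrolled are arithmetically right for one two-sided t-test at 0.05. They do not establish 0.80 power and 5% error for a hypothesis about burnout and quality of life measured by seven or eight scores with no stated success rule.

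On the reading closest to the Aims (one score per construct, both required), it is power that is overstated: about 0.64 to 0.72 rather than 0.80. On an unadjusted any-of-seven reading, it is the error rate: about 30% if the scores are independent and 18% at correlation 0.7, rather than 5%.

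These sizes rest on assumed correlations of 0 to 0.7, a two-sided test, 64 evaluable per group and, for power, d = 0.5 on every score. They follow the article's own two-group comparison. How the planned group-by-time ANOVA differs from that comparison is a separate matter.

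**What to change.** Recruitment was still under way when the article was submitted (Trial status). Before any arm-level data are seen:

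1. Name one MBI-GS score and one WHOQOL-BREF score as the two primary endpoints. List the remaining dimensions and domains as secondary.
2. State the success rule. Since the hypothesis is worded with 'and', require both at 0.05, with no alpha split, and restate joint power as about 0.64 to 0.72 at 64 per group, giving the correlation assumed.
3. If either endpoint is meant to count, use Holm at a family-wise 0.05 and restate power as about 0.76 to 0.78 per test. The figure of 0.71 belongs to Bonferroni and should not be quoted for Holm.

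The cost is wording in the plan and a registry update, plus a less favourable stated power. No participants need be added if that lower power is openly accepted. Holding 0.80 instead would take about 210 enrolled for both required (independent scores), or 196 for a Bonferroni split over two.

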### Participants and settings

Two types of police officers will be recruited for the POLICE study in two Brazilian metropolitan areas:*Civil Police.* The study center in Porto Alegre will be located in the Police Hall of the State of Rio Grande do Sul. Civil Police main duties are to oversee public order and security, adopt measures necessary to avoid danger or injury to persons and public or private property, ensure the administration of criminal offenses, including execution of arrest warrants and requisitions requested by the judicial branch.*Civil Guard.* The study center in São Paulo will be located in the headquarters of Unifesp Santo Amaro Campus. Civil Guard fundamental duties include the protection of goods, services and municipal facilities, as well as patrolling areas and preventive policing.

### Eligibility

To be admitted in the study, participants will meet the following inclusion criteria: (a) be active police officers; (b) 21 to 65 years old; (c) available to attend 8 sessions; (d) willing to voluntarily participate. Exclusion criteria include: (a) previous involvement in any mindfulness-based intervention or being practicing mindfulness regularly in the last 3 months, or one of the following diagnosis, as evaluated by a trained psychologist using the Mini International Neuropsychiatric Interview (MINI) [43]: (b) major depressive episode (current); (c) manic or hypomaniac episode (current); (d) psychotic syndrome (current or past); (e) substance use disorder (past 12 months, except tobacco); (f) risk of suicide.

### Recruitment, procedures and randomization

We will recruit 160 police officers from 2016 to 2018. Recruitment will be conducted using advertisements within the participating police organizations (Internet, social media, posters). Interested officers will contact the research team. After the first screening by phone or e-mail, potential participants will be scheduled for a face-to face interview, where they will be provided with detailed information about the study, fill the informed consent form and inclusion/exclusion criteria will be evaluated. Successful volunteers will be randomly assigned to the MBI or waitlist. Randomization will be implemented using sealed envelopes by an independent researcher who will be unaware of the characteristics of the study and will have no involvement in the trial or access to the study data. Participants allocated to the waitlist will not participate in any active intervention during this study period; however, they offered the MBI program after the 6-month follow-up. Each intervention and waitlist control group will be composed of around 20 participants. Due to the nature of the intervention, this will be a single-blind study, in which the outcomes assessment will be blind, but participants will be aware of their group assignment.

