### Assessments and outcomes

The three assessment points—baseline, post-intervention and follow-up—will occur over the two weeks preceding the intervention, the two weeks after the intervention, and six months after the intervention, respectively (see Table 2). The baseline assessment also will include sociodemographic and clinical characteristics. Survey Monkey Software [53] will be used for data collection. During research visits the participants will enter responses directly into the electronic system. Whenever this may not be possible, the research team will provide sheets of paper and the answers will be uploaded by the team. All instruments have been translated to Portuguese with reliable psychometric properties [54–64].

**Table 2 Tab2:** Assessments as a function of time points (according to 2013 SPIRIT figure guidelines)

Measure	Target	T0	T1	T2
		Baseline	Post-intervention (8 weeks)	Follow-up (6 months)
*MINI*	Psychiatry disorders	x		
*WHOQOL-BREF*	Quality of life	x	x	X
*MBI-GS*	Burnout symptoms	x	x	X
*PSQ*	Stress	x	x	X
*HADS*	Anxiety and depression symptoms	x	x	X
*CD-RISC-25*	Resilience	x	x	X
*MAAS*	Mindfulness trait	x	x	X
*EQ*	Decentering	x	x	X
*SCS*	Self-compassion	x	x	X
*GHQ-12*	Mental well-being	x	x	X
*BCSQ-12*	Burnout subtypes	x	x	X
*WHOQOL-SRPB-BREF*	Spirituality, religiosity and personal beliefs	x	x	X
*DUREL*	Religiosity	x	x	X

*MINI* Mini International Neuropsychiatric Interview, *WHOQOL-BREF* World Health Organization Quality of Life bref, *MBI-GS* Maslach Burnout Inventory - General Survey, *PSQ* Police Stress Questionnaire, *HADS* Hospital Anxiety and Depression Scale, *CD-RISC-25* Connor-Davidson-25 Scale of Resilience, *MAAS* Mindful Attention Awareness Scale, *EQ* Experience Questionnaire, *SCS* Self Compassion Scale, *GHQ-12* The 12-Item General Health Questionnaire, *BCSQ-12* Burnout Clinical Subtype Questionnaire, *WHOQOL-SRPB-BREF* World Health Organization Quality of Life Bref -Spirituality, Religiousness and Personal Beliefs, *DUREL* Duke University Religion Index

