
To explore the feasibility and adherence of MBHP among police officers, the frequency of attendance to the sessions will be assessed. At the post-intervention and the six-month follow-up evaluations we will address mindfulness practice parameters such as type, frequency and length of personal meditative practice through a questionnaire created by our research group [79].

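### Outcome assessment is described as blind, but every between-arm efficacy outcome after baseline is self-reported by officers who know their allocation

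*Protocol article*

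**What the plan says.** All references are to the protocol article.

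- **Blinding** (Recruitment, procedures and randomization): "this will be a single-blind study, in which the outcomes assessment will be blind, but participants will be aware of their group assignment". The article does not say which role is blind.
- **Data capture** (Assessments and outcomes): "During research visits the participants will enter responses directly into the electronic system". When that is not possible, "the research team will provide sheets of paper and the answers will be uploaded by the team".
- **Primary outcomes** (Primary outcomes measures): WHOQOL-BREF is the short form of an instrument "which captures many subjective aspects of quality of life". MBI-GS asks officers about their own feelings about work, on a frequency scale.
- **Interview** (Eligibility): the psychiatric exclusions are assessed by a trained psychologist using the MINI, which Table 2 marks at baseline only.
- **Control** (Recruitment, procedures and randomization): "Participants allocated to the waitlist will not participate in any active intervention during this study period".
- **Attendance** (end of Secondary outcomes measures): "the frequency of attendance to the sessions will be assessed", for the purpose of feasibility and adherence.
- **Limitations** (Discussion): the waitlist comparator is acknowledged as a possible source of overestimated effects. Self-report by unblinded participants is not mentioned.

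**The concern.** Blinded outcome assessment protects a trial when someone other than the participant judges the outcome and does not know the arm. Here the article claims that protection, while its description of the measurements leaves nobody in that position.

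A reader who takes the sentence at face value may credit the trial with control of detection bias that it lacks for its efficacy outcomes. The design makes this matter. Officers volunteer in response to advertisements, know whether they received the training, and rate their own burnout and quality of life against a comparator with no active intervention. Any effect of expectation on how they answer goes into the between-arm difference and cannot be separated from an effect of the programme.

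**Working it through.** The check is a comparison of the blinding sentence with the list of outcomes and the account of who produces the data.

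**Step 1. Instruments in Table 2.** There are 13: MINI, WHOQOL-BREF, MBI-GS, PSQ, HADS, CD-RISC-25, MAAS, EQ, SCS, GHQ-12, BCSQ-12, WHOQOL-SRPB-BREF and DUREL.

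**Step 2. Rated by an assessor.** Only the MINI, a structured diagnostic interview. It is marked at T0 and not at T1 or T2, and it serves eligibility.

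**Step 3. Used at T1 and T2.** 13 − 1 = 12. Both primary outcomes are among them.

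**Step 4. Who answers these 12.** The outcome sections describe them as questionnaires or rating scales. Assessments and outcomes says that participants key in their own responses, with paper as the fallback. On the paper route the team transfers the answers; no rating by staff is described.

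**Step 5. Other efficacy endpoints.** No clinician-rated, biological or administrative efficacy endpoint is named. Two further items are collected after baseline:

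- the personal-practice questionnaire at T1 and T2, which is also participant-reported;
- session attendance, which need not be self-reported but measures feasibility and adherence and is not an efficacy comparison between arms.

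**Step 6. Result.**

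| Post-baseline instruments in Table 2 | Count |
|---|---|
| Answered by the participant, who knows the arm | 12 of 12 |
| Rated by an assessor, blind or not | 0 of 12 |

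**Step 7. Stated figures.** The sample size does not depend on the blinding claim, and it reproduces. A two-sample t-test with d = 0.5, two-sided alpha 0.05 and power 0.80 needs 63.77 per group, rounded up to 64 (power at 64 is 0.801). The article does not state sidedness, but the two-sided value matches. Then 2 × 64 = 128, and 128 / (1 − 0.20) = 160. Correcting the blinding sentence changes none of these.

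**The case against.** The strongest reply is that the sentence does not say who is blind. There are research visits, and staff hand out paper forms and upload answers. Keeping those staff unaware of allocation is an ordinary meaning of such a sentence, and nothing in the article says that they know the arm. This stands in part: staff blinding may well be intended, and it could limit prompting or transcription errors. It does not rescue the claim as written, because the staff rate nothing and an officer's own answer is not blinded by a blind colleague in the room. Staff who handle answers about personal meditation practice might also infer the arm.

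Second, nothing is hidden: the same sentence admits that participants know their arm, and the outcome sections show that they complete the questionnaires. That is true, and a careful reader can work it out. The statement that outcome assessment is blind still needs correcting.

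Third, the Discussion already concedes that a waitlist may inflate effects. That covers the choice of comparator but not the route through unblinded self-report, and it leaves the blinding sentence uncorrected.

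Fourth, participants cannot be blinded to a waitlist. Agreed; the point asks only for an accurate description.

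Some stronger readings are tempting but not supported:

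- *No one in the trial is blinded, so it must be labelled open-label.* The article does not exclude blinded staff, so that label could itself be wrong.
- *Every measurement after baseline is self-reported.* Session attendance need not be.
- *The registry entry is wrong too.* The article gives only its number and date, not what it says on masking.
- *The bias can be put in standard-deviation units.* The article has nothing from which to calibrate it.
- *The article is at fault for not mentioning coded arms.* That detail is commonly left to a full protocol or analysis plan. Coding is proposed here only as a place where blinding is possible.

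**Conclusion.** The point holds for efficacy outcomes compared between arms. The article claims blind outcome assessment, but 12 of 12 instruments used after baseline, including both primary outcomes, are reported by participants who know their allocation, and the one assessor-rated tool is not used after baseline. Blinding of staff, if it exists, does not change this.

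The conclusion rests on the article's own table and its account of data entry. It assumes that the data-entry description applies to all 12 questionnaires, since no exception is given. The direction of concern is an effect that may include expectation; its size is unknown. No sample-size figure changes and no planned analysis is invalidated. The correction is worth making because the sentence offers a safeguard that the efficacy measurements do not have.

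**What to change.** 1. Under Recruitment, procedures and randomization, replace the blinding sentence with a statement that all efficacy outcomes are reported by participants who know their allocation.
2. Limit any remaining blinding claim to named roles that are actually blinded, for example visit or data-entry staff, where existing staffing allows it. The article does not say whether recruiters, visit staff and interventionists are different people, so this has to be confirmed first.
3. Run the primary analysis on coded arms.
4. In the Discussion, beside the waitlist limitation, state that the estimated effect is against an unblinded waitlist on self-report and may include expectation effects.

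The cost is a few sentences and coded arm labels for the analyst. The design will read as slightly less well protected than it does now. Outcomes, sample size, randomization and the planned models stay as they are.
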